### Statistics

For the efficacy endpoint, a land-mark analysis that might be more appropriate for immunotherapy was used to calculate the sample size. In the ABC2 study, the 12- month PFS, calculated from the start of chemotherapy, was 23% [15]. In this study, this would be equivalent to 8-month PFS as eligible patients will be recruited following 4 cycles of cisplatin-based chemotherapy administered over a period of 4 months. This study conservatively aims to increase the 12-month PFS, as defined by the ABC-02 study, to 42%. The sample size calculation comparing a single proportion to a known proportion (42%) yields a sample of 34 patients taking into consideration Type 1 error of 0.05 and power of 0.8. Adding that drop-out or treatment withholding due to patient decision or unacceptable AE occurrence can take place, an additional 15% will be added to yield a total sample size of 40 patients. PFS will be estimated using Kaplan–Meier methods. Median PFS and the PFS rate at 8 months and corresponding 95% CIs will be presented. PFS will be defined for all patients as the time between the date the patient is enrolled in the study and the date on which imaging reveals disease progression or the patient dies, whatever is earlier, and the last follow-up date, in case neither disease progression nor death has occurred. Patients without progression or death will be censored at the last assessment. PFS will be analyzed for all the patients. Exploratory variables will be analyzed according to their scale of measurement by using mean ± standard deviation or frequency distribution for numeric and categorical variables respectively. Frequency distribution for AEs and SAEs will be presented per cycle and per patient. Similarly, this will be done for the SAE of Grade 3 or above combined.

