### Treatment schedule

Week 1 (D1) ± 3 days: Nivolumab administration cycle 1.Week 2 (D8-D12) ± 3 days: start of SBRT for 3–5 fractions.Week 3 (D20 or D22) ± 3 days: percutaneous core biopsy 2 weeks after the end of SBRT.Week 4 (D29) ± 3 days: Nivolumab administration cycle 2.Week 8 (D57) ± 3 days: Nivolumab administration cycle 3.Week 12 (D85) ± 3 days: Nivolumab administration cycle 4.Week 16(D110-113) ± 3 days: Nivolumab administration cycle 5 and CT scan of the chest (to be ordered only in case of metastasis), abdomen and pelvis.

In case of disease progression: treatment will be withheld. Follow-up visits will be scheduled every 3 months. In case of stable disease or partial response: Nivolumab 480 mg administration every 4 weeks and disease evaluation by CT every 4 months of Nivolumab until disease progression.

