### Outcomes

Tumor assessments will be done using CT scans of the abdomen, pelvis and chest.

PFS is defined for all patients as the time between the date the patient is enrolled in the study and the date on which imaging reveals disease progression or the patient dies, whatever is earlier, and the last follow-up date, in case neither disease progression nor death has occurred. Patients without progression or death will be censored at the last assessment regarding progression. PFS will be analyzed for all patients. OS is defined as the time from enrollment to death from any cause. TRR is the assessment of the tumor burden (TB) after a given treatment, duration of response is the time from response to progression/death. The following biomarkers will be evaluated: CD3 + , CD4 + and CD8 + T cell infiltration, and changes in PD-L1 expression following 1 cycle of Nivolumab and SBRT. AEs will be reported and graded according to NCI-CTCAEv5, within 24 h of knowledge of the event, to Bristol Myers Squibb (BMS) and the ethics committees, as per local rules and regulations. Quality of life will be assessed using the general questionnaire for the functional assessment of cancer therapy (FACT-Hep, English version 4 of 16 November 2007 or Arabic version 4 of 02 July 2018 or French version 4 of 19 February 2010).

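### The primary PFS endpoint carries two incompatible end dates for event-free patients, and the CT schedule leaves assessment unclear after nivolumab stops without progression

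*Protocol article*

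**What the plan says.** The 8-month PFS rate is a primary endpoint, estimated by Kaplan–Meier and shown with a 95% CI. Statistics defines PFS from enrolment to progression on imaging or death, "and the last follow-up date, in case neither disease progression nor death has occurred". It then says: "Patients without progression or death will be censored at the last assessment". Outcomes repeats the definition, last follow-up date included, and gives the censoring rule more exactly: "Patients without progression or death will be censored at the last assessment regarding progression". Both sections say that all patients are analysed for PFS.

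Treatment schedule places the first on-study CT at week 16: "Nivolumab administration cycle 5 and CT scan of the chest". After that it has two branches. For stable disease or partial response: "Nivolumab 480 mg administration every 4 weeks and disease evaluation by CT every 4 months of Nivolumab until disease progression". For progression: "In case of disease progression: treatment will be withheld. Follow-up visits will be scheduled every 3 months". Trial duration says that patients are followed until death.

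Statistics expects some patients to stop early: "Adding that drop-out or treatment withholding due to patient decision or unacceptable AE occurrence can take place, an additional 15% will be added".

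**The concern.** The date of last follow-up and the date of the last tumour assessment are different dates. A patient can be seen in clinic, or known to be alive, months after the last CT. Carrying that patient to last follow-up keeps them in the risk set as progression-free over a period in which nobody looked for progression. An analysis plan can follow only one of the two sentences, and the article gives no order of precedence.

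The choice matters most for patients whose contact continues while their imaging does not. The likeliest such group is patients who stop nivolumab without progression, and they fit neither branch of the Treatment schedule. The CT interval is expressed in months of nivolumab, yet its stated end is progression, and PFS is to cover all patients. It is unclear whether scans continue for them.

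At stake is the main result of a single-arm trial of 40 patients, read against a fixed historical 23%. No concurrent arm would share the same error.

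**Working it through.** **1. The plan's own figure.** Null 23%, target 42%, type 1 error 0.05, power 0.80 (Statistics). With the normal approximation, one-sided:

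n = [(1.645·√(0.23·0.77) + 0.842·√(0.42·0.58)) / 0.19]² = 33.98, so 34.

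34/0.85 = 40, and 34 × 1.15 = 39.1, also 40. The stated 34 and 40 reproduce. No censoring date enters the formula, so the point leaves the sample size alone.

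**2. How far apart the dates can be.** CT falls at about day 113 and then every 4 months, so the second is at about day 113 + 112 = 225. Month 8 is about day 243.5. Contact can outrun the last CT by one interval, about 4 months, and by more if a scan is missed or scanning ends, because follow-up runs until death. The 8-month rate rests on the CTs near days 113 and 225. If every patient has both scans, the two dates give almost the same 8-month rate. They separate when a scan is missing and contact goes on.

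**3. Simple bounds.** The 15% allowance is 40 − 34 = 6 patients. Assume that all six stop early without a further CT, and that x of the other 34 are progression-free at 8 months.

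| Handling of the six | x = 8 | x = 14 |
|---|---|---|
| Carried past month 8 as progression-free | 14/40 = 35.0% | 20/40 = 50.0% |
| Censored before any event | 8/34 = 23.5% | 14/34 = 41.2% |
| All six in fact progressed | 8/40 = 20.0% | 14/40 = 35.0% |

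These are extremes and not forecasts. The middle row equals the Kaplan–Meier estimate only if all six are censored before the first event.

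**4. Simulation.** Every input here is an assumption: exponential progression with true 8-month PFS of 23% or 42%; 15% or 30% of patients assigned a stop between days 29 and 113, effective only if it precedes progression; no CT after that stop; CT at days 113, 225, 337 and so on for everyone else; mean 180 days from progression to death; stoppers with the same or twice the hazard of the others; data cut-off between days 365 and 720. The table gives the 8-month Kaplan–Meier rate minus the rate with CT continued in everyone, in percentage points. Monte Carlo error is about 0.5 to 0.7 points.

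| Rule for event-free patients | 15% assigned to stop | 30% assigned to stop |
|---|---|---|
| Last follow-up | +3 to +4 | +6 to +7 |
| Last assessment, later deaths counted | 0 to +2 | +1 to +5 |
| Last CT, later deaths ignored | −2 to +1 | −4 to +1 |

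One cell as an example: true rate 42%, 15% stopping, equal hazards, last follow-up: 47.9% − 44.7% = +3.2. The third rule is shown only for comparison, since the article counts death as an event.

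Under these inputs the excess comes entirely from patients whose scans end. With CT continued, every event-free patient has a scan on day 337 or later, and the two dates give the same 8-month rate.

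**5. Worst case for patients who stop.** 14/34 has an exact 95% CI of 24.6 to 59.3%, which excludes 23%. 14/40 has 20.6 to 51.7%, which does not. The lower 90% limits, 26.9% and 22.6%, also fall on either side of 23%. But 14 is the smallest count out of 34 whose 95% lower limit clears 23% (13/34 gives 22.2%). If two of the six are progression-free, the result is 16/40 with a lower limit of 24.9%, and the contrast disappears. On the 90% interval one of six is enough (15/40, 24.7%).

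**The case against.** The strongest reply is that the wording has a natural reading. The explicit censoring sentence follows the definition, Outcomes adds that the assessment is one of progression, and this is the usual convention, so the last follow-up date is loose drafting. That is plausible. It does not remove the conflict, because the last follow-up date stands in the definition itself, in two sections.

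A reader might go further and infer that patients who stop nivolumab for toxicity or by choice are informatively censored in the primary analysis, and that both dates push PFS upward. The documents do not support that:

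- No sentence ends CT when nivolumab stops, and none makes stopping a censoring event. The phrase "disease evaluation by CT every 4 months of Nivolumab until disease progression" names progression as its end, and it describes patients who continue treatment.
- The 15% is an enrolment allowance that lists drop-out and treatment withholding side by side. It is not an exclusion or censoring rule.
- Fig. 1 and the full protocol are not shown and may hold an off-treatment imaging calendar.
- Death remains an event, so a patient who stops and then dies is counted.
- The two mechanisms are alternatives. Under last follow-up, patients who stop are not censored early. Under last assessment they may be, and the direction then depends on why they stopped and whether scans go on.
- The contrast of 14/34 with 14/40 is a worst case at a threshold, and the article states no decision rule based on a confidence limit clearing 23%.

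All of this stands, and it limits the second part of the point to a risk. The contradiction in the censoring date is untouched.

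**Conclusion.** The point holds for the censoring date. Statistics and Outcomes each give two incompatible end dates for event-free patients on a primary endpoint, and one of them credits unimaged time as progression-free. The bias from that date is upward: about 3 to 4 points on the 8-month rate when 15% are assigned an early stop, and 6 to 7 when 30% are. Those sizes rest on the assumed inputs, above all that CT ends with nivolumab. If scans continue on schedule, the difference at 8 months is small or nil.

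The article also leaves open whether tumour assessment continues after stopping without progression. Informative censoring of these patients is a risk under that wording and not an established fact. Under last-assessment censoring its direction is uncertain. The 14/34 against 14/40 comparison should be read as a bound only. The sample size of 34, inflated to 40, is unaffected.

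**What to change.** 1. In Statistics and in Outcomes, delete the last follow-up date from the PFS definition. Censor event-free patients only at the last evaluable tumour assessment, with death still an event.
2. State that stopping nivolumab is not in itself a censoring event for PFS.
3. In Treatment schedule, reconcile the CT interval counted in months of nivolumab with its stated end at progression and with the analysis of PFS in all patients. The text should make clear whether tumour assessment continues on the calendar schedule for patients who stop without progression. If Fig. 1 or the full protocol already settles this, a cross-reference is enough.

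The cost is wording in three places and possibly a slightly lower 8-month estimate than last-follow-up censoring would give. If the answer to item 3 is that imaging continues, a handful of off-treatment patients keep the CT schedule already planned.

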### Eligibility criteria

For patient inclusion, all of the following criteria must be met:

Signed and dated informed consent form.Patients aged ≥ 18 years.Pathologically (histologically or cytologically) and radiologically confirmed diagnosis of non-resectable locally advanced or metastatic or recurrent intrahepatic or extrahepatic CCA within 90 days of registration.Patients who have SD or PR following 4 cycles of cisplatin-based chemotherapy.ECOG performance score < 3.An estimated life expectancy of more than 3 months.Have adequate hematologic and biochemical function by meeting the following:Total bilirubin acceptable level ≤ 1.5 × the institutional upper limit of normal (ULN) range;Aspartate aminotransferase (AST) and alanine aminotransferase (ALT) acceptable levels up to 5 × ULN range;Serum urea and serum creatinine acceptable levels up to 1.5 × ULN range;Calculated glomerular filtration rate ≥ 45 mL/min according to the Chronic Kidney Disease Epidemiology Collaboration equation (or local institutional standard method). Negative serum or urine pregnancy test at screening for women of childbearing potential who are sexually active.Highly effective contraception for both males and females of child-bearing potential who are sexually active throughout the study and for at least 5 months and 7 months after the last nivolumab treatment administration, respectively.Candidate for percutaneous biopsy as per tumor location evidenced by CT scan and interventional radiologist.

### Exclusion criteria

Patients who have progression following 4 cycles of cisplatin-based chemotherapy evidenced by CT scan as per RECIST 1.1.Active brain metastases or leptomeningeal metastases.Prior organ transplantation or allogenic stem-cell transplantation.Known prior severe hypersensitivity to IMP or any component in its formulations, including known severe hypersensitivity reactions to monoclonal antibodies (NCI-CTCAE v4.03 Grade ≥ 3).Active infection requiring systemic therapy within 28 days before the first dose of study treatment (e.g., urinary tract infection).Known history of testing positive for the human immunodeficiency virus or known acquired immunodeficiency syndrome.Evidence of liver cirrhosis.Current use of immunosuppressive medication, except for the following:Intranasal, inhaled, topical steroids, or local steroid injection (e.g., intra-articular injection);Systemic corticosteroids at physiologic doses ≤ 10 mg/day of prednisone or equivalent;Steroids as premedication for hypersensitivity reactions (e.g., CT scan premedication).Active autoimmune diseases that might deteriorate upon receiving an immune-stimulatory agent.Conditions such as vitiligo, psoriasis, diabetes type I, or hypo- or hyper-thyroid diseases not requiring immunosuppressive treatment are eligible.Commonly excluded conditions include: Addison’s disease, thyroiditis/Hashimoto’s thyroiditis, systemic lupus erythematosus, Sjogren’s syndrome, scleroderma, myasthenia gravis, Goodpasture’s syndrome, and Grave’s disease.Hepatic insufficiency manifesting as clinical jaundice, hepatic encephalopathy, and/or variceal bleed within 60 days prior to study entry.Transmural myocardial infarction within 6 months of enrollment; provided that anti-platelets cannot be stopped to perform percutaneous biopsy.Congestive heart failure (≥ New York Heart Association Classification Class II) requiring hospitalization within the last 6 months provided that anti-platelets cannot be stopped to perform percutaneous biopsy.Serious cardiac arrhythmia requiring medical treatment provided that anti-platelets cannot be stopped to perform percutaneous biopsy.Recent cerebral vascular accident/stroke within 6 months of enrollment provided that anti-platelets cannot be stopped to perform percutaneous biopsy.End-stage renal disease requiring dialysis.Other severe acute or chronic medical conditions including immune colitis, inflammatory bowel disease, immune pneumonitis, pulmonary fibrosis, or psychiatric conditions including recent (within the past year) or active suicidal ideation or behavior.Treatment with an investigational agent within 28 days before the first dose of study treatment.Prior treatment with any drug or antibody (anti-PD-1, anti-PD-L1, anti-PD-L2, anti-CD137, or anti-CTLA-4 antibody) targeting T cell co-stimulation or checkpoint pathways.Patients suspected by the physician that he/she will not be compliant to the protocol conduct.Pregnant women are excluded from this study; breastfeeding should be discontinued.Patients participating in another clinical trial.Patients not willing to sign the consent form.Any psychiatric condition that would prohibit the understanding or rendering of informed consent.Legal incapacity or limited legal capacity patients receiving other oncology specific medication not authorized in the protocol.

### Treatment plan (Fig. 1)

**Fig. 1 Fig1:**
[figure not shown]
Treatment plan of the study, including all visits, cycles, labs and tests needed for monitoring

Nivolumab 480 mg IV over 60 min:Every 4 weeks;Until disease progression or unacceptable occurrence of AESBRT to 1–2 sites of disease starting around 7 days following the first Nivolumab dose:A total of 30 Gy in 3–5 fractions (depending on the target size and proximity to critical structures);The lesions treated with SBRT will be selected on individual basis using the following clinical overall guide:Symptomatic (pain or obstruction) lesions will be prioritized for SBRTTreatment safety and proximity to critical structures will be taken into consideration in choosing SBRT targetsCT-based treatment planning will be performed for all participants. Whenever possible/deemed necessary, metal fiducials will be placed for intrahepatic targets. Image guided radiotherapy will be performed with cone beam CT scans taken prior to each fraction delivery.

### Treatment schedule

Week 1 (D1) ± 3 days: Nivolumab administration cycle 1.Week 2 (D8-D12) ± 3 days: start of SBRT for 3–5 fractions.Week 3 (D20 or D22) ± 3 days: percutaneous core biopsy 2 weeks after the end of SBRT.Week 4 (D29) ± 3 days: Nivolumab administration cycle 2.Week 8 (D57) ± 3 days: Nivolumab administration cycle 3.Week 12 (D85) ± 3 days: Nivolumab administration cycle 4.Week 16(D110-113) ± 3 days: Nivolumab administration cycle 5 and CT scan of the chest (to be ordered only in case of metastasis), abdomen and pelvis.

In case of disease progression: treatment will be withheld. Follow-up visits will be scheduled every 3 months. In case of stable disease or partial response: Nivolumab 480 mg administration every 4 weeks and disease evaluation by CT every 4 months of Nivolumab until disease progression.

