## Methodology

### Objectives

This trial aims to assess the efficacy and safety of nivolumab with SBRT after induction chemotherapy in patients with CCA. The primary endpoint is the PFS at 8 months and DCR in patients with non-resectable locally advanced or metastatic or recurrent intrahepatic or extrahepatic CCA following Nivolumab/SBRT treatment.

The secondary endpoints are OS, tumor response rate (TRR), duration of response, evaluation of biomarkers: CD3 + , CD4 + and CD8 + T cell infiltration, changes in PD-L1 expression following 1 cycle of nivolumab and SBRT, AE and quality of life.

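### The Treatment schedule limits the Week 16 chest CT to cases of metastasis while Outcomes includes the chest without restriction; if the schedule is followed, chest-only progression in non-metastatic patients is found late or not at all

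*Protocol article*

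**What the plan says.** All references are to the protocol article.

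- **Treatment schedule, Week 16 (D110-113):** a "CT scan of the chest (to be ordered only in case of metastasis), abdomen and pelvis". No earlier on-study CT for disease evaluation is listed.
- **Treatment schedule, afterwards:** for stable disease or partial response, "disease evaluation by CT every 4 months of Nivolumab until disease progression". The body regions are not restated.
- **Outcomes:** "Tumor assessments will be done using CT scans of the abdomen, pelvis and chest", with no restriction by stage or visit.
- **Outcomes, PFS event:** "the date on which imaging reveals disease progression or the patient dies, whatever is earlier". For patients with no event, "Patients without progression or death will be censored at the last assessment regarding progression".
- **Objectives:** "The primary endpoint is the PFS at 8 months and DCR in patients with non-resectable locally advanced or metastatic or recurrent" disease, so both parts of the primary endpoint rest on these scans.
- **Eligibility criteria:** "non-resectable locally advanced or metastatic or recurrent intrahepatic or extrahepatic CCA within 90 days of registration". Patients without metastasis can therefore enter. Their expected share is not given.

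**The concern.** The same imaging-based endpoint has two imaging extents. For a patient with metastasis the two rules agree. For a patient without, the schedule read literally omits the chest at Week 16 and Outcomes includes it. The study is multicentre, so sites could reasonably follow different sections.

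A new lesion in a region that is not imaged cannot be recorded as progression. The patient then counts as progression-free until something else is found or the patient dies. That error has one direction: it delays or removes events. It would raise observed 8-month PFS, DCR and duration of response, and would tie ascertainment to disease stage and site. In a single-arm study no concurrent group shares the error.

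**Working it through.** **1. The two rules side by side**

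| Patient | Treatment schedule, Week 16 | Outcomes |
|---|---|---|
| With metastasis | chest, abdomen, pelvis | chest, abdomen, pelvis |
| Without metastasis (locally advanced or non-metastatic recurrent) | abdomen, pelvis | chest, abdomen, pelvis |

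The second row is the conflict. Nothing in the text shown says which section governs.

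**2. The plan's own figure**

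Inputs from Statistics: a reference rate of 23% ("the 12- month PFS, calculated from the start of chemotherapy, was 23" per cent, taken as equivalent to 8 months from enrolment here), a target of 42%, type I error 0.05 and power 0.8. Sidedness is not stated. With null and alternative variances:

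n = [(z_a·√(p0(1−p0)) + z_b·√(p1(1−p1))) / (p1−p0)]²

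One-sided: [(1.645·√(0.23·0.77) + 0.842·√(0.42·0.58)) / 0.19]² = [(0.692 + 0.415) / 0.19]² = 33.98, so 34. Then 34/0.85 = 40. Both stated numbers reproduce. A two-sided 0.05 gives 42.6, so 43, which does not match. Making the imaging uniform leaves 34 and 40 unchanged.

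**3. Upper bound on the shift in 8-month PFS**

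Two quantities are not in the documents and are assumed:

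- f, the share of patients without metastasis: 20% to 50%
- q, the share of their progressions by 8 months that are visible only in the chest: 5% to 15%

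If every such progression stays hidden past 8 months, and non-metastatic patients have events at the same 77% rate as the rest:

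observed PFS = 0.23 + 0.77·f·q

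| f | q | f·q | Added points | Observed PFS | Patients in 40 |
|---|---|---|---|---|---|
| 20% | 5% | 0.010 | 0.8 | 23.8% | 0.3 |
| 50% | 5% | 0.025 | 1.9 | 24.9% | 0.8 |
| 20% | 15% | 0.030 | 2.3 | 25.3% | 0.9 |
| 50% | 15% | 0.075 | 5.8 | 28.8% | 2.3 |

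**4. What that would mean for a 34-patient test**

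The article states no decision rule, so this is only an illustration. An exact one-sided binomial test of 23% at 0.05 with n = 34 needs 13 or more event-free patients, and its type I error is 0.033. At the observed rates above, in table order, the chance of reaching 13 when the true rate is 23% becomes 0.042, 0.060, 0.066 and 0.152.

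**5. Why step 3 is a ceiling**

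Four calendar months is about 122 days, so the second CT falls near D232-235. Eight months is about 243.5 days, or about D244 counted from D1. If the second scan covers the chest and enrolment is close to D1, a lesion missed at Week 16 is found before the landmark and still counts against 8-month PFS. The margin is roughly 9 to 12 days. PFS runs from enrolment, so a longer gap between enrolment and D1, or a scan late in its window, uses that margin up. Later progression in the abdomen or pelvis, or death, by 8 months would also restore the event.

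**The case against.** A reader might infer that lung progression will be missed and that PFS in the locally advanced subgroup is inflated. The documents do not support that, for these reasons.

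- **It is conditional.** If sites follow Outcomes, nothing is missed. The restricting words could also be read as covering metastasis suspected during the study, not only baseline stage. This stands. However, ascertainment would then depend on clinical suspicion, which still differs from Outcomes.
- **The restriction is written for Week 16 only.** A second CT that includes the chest could catch the lesion just before 8 months, so the event may be delayed and not lost. This stands, and it is why the figures are an upper bound. The coverage of that scan is not stated, so it cannot be relied on. If DCR is read at Week 16, the later scan would not correct it.
- **The figures rest on assumptions.** Nothing in the documents supports the ranges for f and q or the common event rate. This stands.
- **It is not a subgroup result.** No subgroup PFS analysis is described, so the error would enter the overall estimate. Non-metastatic recurrent patients are affected too.
- **The comparison with the historical control is unknown.** The article does not say how the chest was imaged in the ABC-02 trial. Missed lesions raise PFS here in absolute terms, but whether they bias the comparison cannot be judged from this document.
- **The treatment-plan figure is not shown** and may settle the extent. It would not remove the conflict between the two sections of text.

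**Conclusion.** The contradiction is certain: both sentences are current text, and they give different imaging for patients the trial can enrol. The consequence is conditional. If the schedule is followed as written, chest-only progression in non-metastatic patients is not seen at the first on-study assessment, and the only possible effect is upward on observed PFS, DCR and duration of response in the overall analysis.

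The documents cannot establish the size. Under the assumptions in step 3, the ceiling is 0.8 to 5.8 percentage points on a true 23%, or about 0.3 to 2.3 patients in 40. The low end is negligible. The high end would matter for a decision based on 34 evaluable patients. The point should be corrected because it touches the primary endpoint, its direction is favourable to the treatment, and the correction is simple. It does not show that the trial's PFS is wrong.

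**What to change.** Reconcile the Treatment schedule with Outcomes so that one stated imaging extent applies to every patient at baseline, at Week 16 and at each later 4-monthly CT, whatever the stage at entry. State the extent for the later scans explicitly, and check that the treatment-plan figure agrees. Outcomes already names abdomen, pelvis and chest for tumour assessment.

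Cost: a short text change and no change to the sample size of 34 evaluable and 40 enrolled. If the Outcomes extent is kept, patients without metastasis have a chest acquisition added to CT sessions that are already planned, at each assessment. If some patients have already been assessed under the narrower rule, record which scans included the chest so that the PFS and DCR results can be read with that in view.
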